## **7 Sample size calculation**

Using A'Hern's single stage phase II trial design and  $\alpha=0.05$  and power=80%, 25 patients are needed to distinguish between a averted laparotomy rate of 30% (worth exploring in a phase III trial) and 10% or less (unacceptable outcome) (10). Therefore, a total of 25 patients will be included. This requires at least 6 averted laparotomies to reach the positive endpoint.

## **8 Patient selection criteria**

### **8.1 Inclusion criteria**

- 18 years or older;
- Patients with pancreatic or periampullary cancer undergoing resection with curative intent;
- Absence of any psychological, familial sociological or geographical condition potentially hampering compliance with the study protocol and follow-up schedule; those conditions should be discussed with the patient before registration in the trial;
- Before patient registration, written consent must be given according to ICH/GCP, national and local regulations.

### **8.2 Exclusion criteria**

- History of allergy to iodine, shellfish or ICG;
- Renal impairment, defined as eGFR > 55;
- Patients with hyperthyroidism;
- Pregnant or lactating woman;
- Any condition that in the opinion of the investigator could potentially jeopardize the health status of the patient.

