|------------------------------------|---------------------------------------------------------------------------------------------------------------------------------------------------------------------------------------------------------------------------------------------------------------------------------------------------------------------------------------------------------------------------------------------------------------------------------------------------------------------------------------------------------------|
|                                    | 
registration in the trial;
 
 
- Before patient registration, written consent must be given according to ICH/GCP, national and local regulations.
 
 
Exclusion criteria:
 
 
- History of allergy to iodine, shellfish or ICG;
 
- Pregnant or lactating woman;
 
- Any condition that in the opinion of the investigator could potentially jeopardize the health status of the patient.
 
 |
| Planned trial interventions | 
In addition to standard-of-care, patients will receive an intravenous injection of 10 mg ICG 24 prior to surgery. During surgery, patients undergo a SL, whereupon inspection, LUS and NIR fluorescence imaging will be performed. A biopsy will be taken from any suspect lesions. Decision to continue the resection is up to the surgeon. Follow-up will last at least 6 months.
                                                                                                                    |
| Statistical design          | 
Using A'Hern's single stage phase II trial design and <math>\alpha=0.05</math> and power=80%, 25 patients are needed to distinguish between an averted laparotomy rate of 30% (worth exploring in a phase III trial) and 10% or less (unacceptable outcome). Therefore, a total of 25 patients will be included. This requires at least 6 averted laparotomies to reach the positive endpoint.
                                                                                                         |

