#### **4 Study design**

All patients planned to undergo explorative or curative surgery for pancreatic or periampullary cancer can be included, provided that they meet the inclusion criteria and none of the exclusion criteria. All patients will receive standard-of-care. This includes a CT-scan < 1 month prior to surgery. Optional imaging, such as (endoscopic) ultrasonography, MRI and FDG-PET, may also be performed if required. In addition, peripheral blood samples (8 mL) will be taken from patients before surgery or chemotherapy. These samples will be analyzed for CTCs, CEA, CA19-9 and bilirubin levels. Patients will receive up to three days before surgery an intravenous injection of 4 ml 2.5 mg/ml ICG (10 mg ICG in total).

The SL procedure starts with visual inspection. The laparoscope is inserted via a subumbilical 10 mm trocar. A second 10 mm port is inserted along the anticipated laparotomy incision to allow LUS under direct vision. Up to two additional 5 mm ports may be necessary to allow exposure of organs and potential palliative surgery. The whole abdomen is inspected, including the parietal and visceral peritoneum, the pelvis, the liver, the porta hepatitis, the gastrohepatic omentum, the duodenum, the transverse mesocolon and celiac region. Secondly, LUS (with or without Doppler) of the primary tumor, liver, portal vein, hepatic artery, lymph nodes and superior mesenteric artery will be performed. NIR fluorescence imaging of the liver surface will be performed lastly. Fluorescence will be divided into rim, partial, full and nonspecific (i.e. artefacts) pattern. Any lesions likely to be metastases are sampled and analyzed, either via a biopsy or via radical resection. In case of multiple lesions with similar appearance on inspection, ultrasound and fluorescence, only one biopsy has to be performed when LUS shows a similar signal in all these lesions. However, when one or more lesions are found solely by NIR fluorescence imaging, multiple small biopsies have to be performed to confirm the diagnosis.

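### Section 8.2 defines renal impairment by an eGFR above 55, so the criterion's label and its inequality contradict each other, and the Summary's exclusion list omits the criterion altogether

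*Protocol*

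**What the plan says.** Protocol section 8.2 lists five exclusions. The second is "Renal impairment, defined as eGFR > 55", with no unit. The third is hyperthyroidism. The last is a discretionary item: "Any condition that in the opinion of the investigator could potentially jeopardize the health status of the patient".

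The Summary (section 2) has its own exclusion list with three items: "History of allergy to iodine, shellfish or ICG", pregnancy or lactation, and the same discretionary item. It has no renal item and no hyperthyroidism item.

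Section 4 makes the list operative: patients planned for surgery can be included "provided that they meet the inclusion criteria and none of the exclusion criteria". No other part of the protocol restates or explains the eGFR cut-off.

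**The concern.** eGFR rises as renal function improves. A criterion named for renal impairment but defined by a value above a cut-off therefore names one group and describes the opposite one. This is a contradiction within a single line. It is not a missing detail that a statistical analysis plan would supply, because eligibility is fixed in the protocol.

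Two things are at stake. The first is who may enter the trial, since the answer depends on which half of the line the reader follows. The second is the trial record: with 25 patients planned, uncertainty over whether enrolled patients were eligible bears on how the result is read and audited. The difference between the two exclusion lists adds to this, because a reader who turns to the Summary for clarification finds no renal rule at all.

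**Working it through.** The point is settled by reading the passages side by side. The only arithmetic is a check that the design figures do not depend on it.

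**1. The two halves of the renal criterion**

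| Patient | By the label (renal impairment) | By the inequality (eGFR above 55) |
|---|---|---|
| eGFR above 55 | the better-function side of the cut-off, so not the group named | excluded |
| eGFR at or below 55 | the poorer-function side of the cut-off, so the group named | not excluded by this line |

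The two columns disagree in both rows, so no value of eGFR gives a consistent answer.

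**2. Consequence under each reading**

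- *Inequality followed.* Section 4 requires that no exclusion be met, so a candidate with eGFR above 55 cannot enter. A candidate at or below 55 passes this line but must still pass the other four exclusions, including the discretionary one.
- *Label followed.* Candidates with eGFR above 55 are enrolled, and each meets the exclusion as its definition is written. Each could be recorded as an eligibility deviation.

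**3. The two exclusion lists**

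| Criterion | Summary (section 2) | Section 8.2 |
|---|---|---|
| Allergy | yes | yes |
| Renal impairment | no | yes |
| Hyperthyroidism | no | yes |
| Pregnancy or lactation | yes | yes |
| Investigator discretion | yes | yes |

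Three of the five items are shared and two appear only in section 8.2. The Summary therefore cannot show which half of the renal line was meant.

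**4. Design figures**

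Section 7 uses "A'Hern's single stage phase II trial design and" one-stage error limits of α = 0.05 and power 80%. It contrasts an "averted laparotomy rate of 30% (worth exploring in a phase III trial") with "10% or less (unacceptable outcome"), and concludes: "Therefore, a total of 25 patients will be included", with success at 6 or more averted laparotomies. Let X be binomial with n = 25:

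- α = P(X ≥ 6 | p = 0.10) = 1 − Σ(k = 0 to 5) C(25, k) · 0.10^k · 0.90^(25−k) = 0.0334
- power = P(X ≥ 6 | p = 0.30) = 1 − Σ(k = 0 to 5) C(25, k) · 0.30^k · 0.70^(25−k) = 0.8065

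A search over n = 15 to 31 finds 25 to be the smallest size that meets both limits, so the stated 25 and 6 reproduce. The inputs are n, the threshold and the two rates. eGFR is not among them, so correcting section 8.2 leaves these figures as they are.

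**The case against.** The strongest reply is that this is a reversed sign that nobody would act on. The words renal impairment show the intent, the trial has a single center, and an investigator would notice at the first candidate. This is plausible, but it does not remove the point. Following the intent informally is exactly what puts enrolled patients in conflict with the written definition. One may argue whether such a patient is truly a deviation, since the two halves of the line give opposite answers. That uncertainty is itself the defect.

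A misprint in the copy of the text cannot be wholly excluded. Against it, the less-than sign for the timing of the CT scan in section 4 is printed normally. The sponsor can check the source at once.

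A summary may also abridge. However, it keeps three of the five exclusions and drops exactly these two, without saying that it is partial.

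Several stronger readings are tempting, and here the objection is right:

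- A reader might infer that every candidate at or below 55 is eligible. The discretionary exclusion in section 8.2 means that this does not follow.
- A reader might infer that a safety purpose is defeated. The protocol never says why renal function is restricted.
- A reader might put a percentage on the candidates wrongly excluded. The protocol gives no eGFR distribution on which to base one.
- A reader might conclude that the Summary should be brought into line with section 8.2. The documents do not show which list is the intended one.

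**Conclusion.** The point holds as an internal contradiction in an operative eligibility rule, together with a mismatch between two exclusion lists. It rests on the printed text of section 8.2 and on the fact that a higher eGFR means better renal function. No assumption about the patient population is needed.

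Its reach is bounded. It concerns one exclusion line, at one center, in a trial of 25. How many patients it touches cannot be stated from the protocol. The primary outcome, the sample size and the decision threshold do not change. It should nonetheless be corrected before further enrolment, because neither reading of the line as it stands leaves a clean eligibility record.

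This review takes no position on which renal rule or cut-off is right.

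**What to change.** The sponsor should:

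1. Amend section 8.2 so that the label and the inequality of the renal criterion agree, confirm the cut-off, and state the unit of eGFR.
2. Reconcile the exclusion lists in the Summary and section 8.2, deciding for both the renal and the hyperthyroidism criteria whether they apply, so that a single list governs.
3. Check anyone already enrolled against the reconciled list and document the result.

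The cost is a short amendment: one line in section 8.2, the matching edit that reconciles the two lists, and a record check covering at most the 25 planned patients. No recalculation of the sample size or threshold is needed.
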